### Discontinuation of Study Intervention

Unexpected discontinuation of study intervention criteria is (1) deterioration of symptoms leading to MSC infusion intolerance; (2) occurrence of adverse events or abnormal laboratory test results leading to MSC infusion intolerance; (3) individual wishes of the subjects; (4) any reasonable situations that require the clinical trial to be halted; (5) researchers' decisions to halt the clinical trial.

Expulsion criteria are (1) non-compliance to the study protocol; (2) other reasons.

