### Adverse Events

Adverse events (AEs) refer to any unwanted symptoms or signs in a clinical investigation subject and do not necessarily have a causal relationship with the applied intervention (29). All AEs will be coded according to the WHO's Adverse Reactions Terminology. At the end of the clinical trial, the intensity and relationship of any AEs with the study intervention will be identified.

If any severe AE (SAE) is encountered, even with extremely low incidence, it will be reported to the trial's principal investigator, the stem cell research ethics committee, and the state supervision agency within 24 h of its occurrence.

There are two types of side effects that need intensive monitoring, side effects during infusion and long-term side effects.

Side effects during infusion include allergic reactions (such as fever, tachycardia, dyspnea) and systematic complications (infection, embolism, and multiple organ failure);

While monitoring long-term side effects, the following items will be tested every 3 months: tumor markers (AFP, CEA, CA199, CA125, CA153, and CA242); complete blood count and urinalysis, liver and kidney function, blood glucose and electrolyte, coagulation tests, tests for infective diseases (HIV, RPR, hepatitis B, and C; tested at baseline, 9 months and 2 years of follow-up), urine HCG; electrocardiogram, chest X-ray or CT, and abdominal ultrasound.

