### Statistical Analysis

The Kolmogorov–Smirnov Z test will be used for checking data normality. Categorical variables will be summarized as counts (percentage) and continuous variables as the means (standard error, SE) or medians (interquartile ranges, IQR), if not normally distributed. For the primary endpoint of the first time of recurrence, survival analysis will be conducted to analyze between-group differences. The Kaplan–Meier estimates for time of recurrence are presented for all groups. Hazard ratios for the comparison of between groups and 95% CIs were calculated with the Cox proportional-hazards model. Prespecified subgroup analyses of the primary outcome were stratified by, EDSS score at baseline, disease duration, age at randomization, the total number of previous relapses, number of relapses 2 years before randomization, and regular treatment. For secondary outcomes, statistical comparisons between the groups will be performed using Student's *t*-test or the Mann–Whitney U test for continuous variables, as well as the chi-square and Fisher's exact tests for categorical variables, as deemed appropriate. Correlations between continuous variables will be assessed by Pearson's correlation coefficient or Spearman's correlation coefficient. All missing data were not imputed in this study.

In this study, two analysis sets will be required. For the safety set (SS) analysis, all safety indicators will be obtained from those who have undergone at least one dose of hUC–MSC infusions. For the effectiveness analysis set, the intention to treat (ITT) analysis set will be used.

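### Expedited safety reporting is triggered by a *severe* adverse event, a term of intensity, so events with a serious outcome but lower intensity have no stated 24-hour route

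*Protocol article*

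**What the plan says.** The Adverse Events section of the protocol article gives a definition, a grading statement and a reporting rule.

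- **Definition:** "Adverse events (AEs) refer to any unwanted symptoms or signs in a clinical investigation subject", whether or not the intervention caused them. All such events are to be coded.
- **Grading:** "At the end of the clinical trial, the intensity and relationship of any AEs with the study intervention will be identified".
- **Expedited reporting:** "If any severe AE (SAE) is encountered, even with extremely low incidence, it will be reported" to the principal investigator, the stem cell ethics committee and the state supervision agency, "within 24 h of its occurrence".

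The same section then lists the long-term monitoring: "While monitoring long-term side effects, the following items will be tested every 3 months: tumor markers", followed by blood, urine, coagulation, infection and pregnancy tests, and ending with "electrocardiogram, chest X-ray or CT, and abdominal ultrasound".

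Three other sections bear on the point. Discontinuation of Study Intervention gives as one criterion "occurrence of adverse events or abnormal laboratory test results leading to MSC infusion intolerance". Trial Quality Assurance says that the protocol will be amended only if an SAE occurs. Statistical Analysis says of the safety set that "all safety indicators will be obtained from those who have undergone at least one dose" of the cell product.

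**The concern.** Severity and seriousness are different attributes of an adverse event. Severity grades how intense the event is. Seriousness asks what it led to: death, threat to life, hospital admission, lasting disability or another medically important consequence. Expedited reporting exists for the second. The article spells out SAE as a *severe* event and makes that the trigger.

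A site that follows the text as printed could record a moderate-intensity event that led to an unplanned admission or lasting disability, grade it correctly, and have no instruction to report it within 24 hours. The ethics committee and the state agency would then not be told promptly about the kind of event for which the rule exists. The SAE term also does a second job, because it decides whether the protocol may be amended.

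A related uncertainty concerns findings made only by a test. The product is an allogeneic cell infusion, and the long-term programme looks for changes in tumour markers, infection serology, organ function and imaging. The definition of an adverse event does not say whether such a finding, without symptoms, is to be entered as one. The six centres could therefore treat the same result differently.

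**Working it through.** No arithmetic applies, and the plan gives no figure to reproduce. The check is a comparison of the text.

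**1. What triggers the 24-hour report?** The article expands the abbreviation itself, as *severe AE*. The grading sentence in the same section treats intensity as an attribute of an event, next to its relationship with the intervention. So intensity is already in use as a concept when the reporting rule is attached to an intensity word. No criterion based on outcome appears in the article.

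**2. What follows for a serious event that is not severe?**

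| Event | Adverse event and coded? | 24-hour report as worded? |
|---|---|---|
| Severe, serious outcome | Yes | Yes |
| Severe, no serious outcome | Yes | Yes |
| Mild or moderate, serious outcome | Yes | No route stated |
| Mild or moderate, no serious outcome | Yes | No |

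Only the third row is a gap, and it concerns the expedited route alone.

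**3. Does the trigger fit the timing of grading?** The report is due within 24 hours of the event, while intensity is said to be identified at the end of the trial. If that sentence describes a final adjudication and sites also grade at onset, the two can coexist, but the article does not say so. A trigger based on outcome would not depend on the answer.

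**4. Where else is the term used?** The amendment rule in Trial Quality Assurance depends on whether an SAE has occurred. Any doubt about what an SAE is carries over to it.

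**5. Are test findings adverse events?**

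- The long-term list has 11 groups: tumour markers; blood count; urinalysis; liver and kidney function; glucose and electrolytes; coagulation; infection tests; urine HCG; ECG; chest X-ray or CT; abdominal ultrasound. All are tests.
- Pointing towards exclusion: the definition names symptoms or signs only, and the discontinuation criteria join adverse events and abnormal laboratory results by *or*.
- Pointing towards inclusion: *signs* is not qualified, and the tests stand under the Adverse Events heading as monitoring for side effects.
- The discontinuation list cannot settle it. Its first item is worsening symptoms, which plainly meet the definition of an adverse event and yet are also listed separately. The list overlaps and does not define terms.

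The status of an abnormal test result is therefore unclear, and no more than that.

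**The case against.** The strongest reply is that *severe* is loose wording for *serious*. It carries the usual abbreviation, and the report goes to the bodies that normally receive serious-event reports. Moreover, this is a journal article condensed from a fuller protocol, which may hold the seriousness criteria and the rule for turning a laboratory result into an adverse event. Their absence here would then be no fault.

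Part of this stands. The wording may well be a slip, and the missing list of criteria is not by itself a finding. But the article does more than omit: it prints an operative rule and attaches it to the wrong attribute. If it is a slip, correcting it costs little. If it is not, the expedited stream has a gap.

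Three stronger readings are tempting, and the documents do not support them.

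- A reader might infer that asymptomatic laboratory or imaging harm falls outside adverse event reporting altogether. The text does not say this. *Signs* can cover objective findings, the tests are placed under Adverse Events, and the safety set covers all safety indicators. Table 1 also schedules physical examination at screening and V2 to V9 and adverse event recording at V1 to V9, so follow-up is not confined to tests.
- A reader might infer that serious but non-severe events drop out of adverse event reporting. They do not: all adverse events are to be coded, and only the 24-hour route is in doubt.
- A reader might infer that dose escalation, dose selection and the data monitoring board would be working from incomplete adverse event data. The Study Design section bases escalation on toxic reactions and dose selection on the balance of efficacy and toxicity, and the board reviews accumulated study data for participant safety. None is limited to events that meet the adverse event definition.

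**Conclusion.** The concern holds in a limited form. The expedited rule is misstated: it depends on intensity when it should depend on outcome, so an event of lower intensity with a serious outcome is coded but has no stated 24-hour route. The amendment rule inherits the same term. Whether an abnormal test result is an adverse event is ambiguous, but such results are not excluded.

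The documents give no event rates by intensity or outcome, so the share of serious events affected cannot be estimated and no figure is offered. The conclusion assumes that sites apply the article as printed. If the full protocol already defines SAE by outcome, the point reduces to correcting the published wording. The change is worth making because it is cheap and concerns participant safety.

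**What to change.** In the Adverse Events section:

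1. Replace *severe AE (SAE)* with *serious AE (SAE)* and define it by outcome: death, threat to life, hospital admission beyond the planned stay for infusion, lasting disability, or another medically important event. The exception for the planned stay is needed because Participant Safety Protection Measures has every infusion given in hospital, with 2 to 4 days of observation afterwards.
2. Keep intensity as a separate grade that does not trigger expedited reporting, and make clear how the end-of-trial grading sentence relates to assessment when the event is recorded.
3. State that clinically significant abnormal laboratory, ECG or imaging findings count as adverse events.

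Then reconcile the wording in Discontinuation of Study Intervention, so that listing abnormal laboratory results next to adverse events does not suggest that they are something else. This is a matter of terminology only; the criteria themselves need not change. The amendment rule in Trial Quality Assurance then takes on the corrected term.

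The cost is revised protocol wording, matching definitions on the case report form, and somewhat more events to record and report. No dose, schedule or sample size is affected.

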### Follow-Up

Primary, secondary, exploratory endpoint events, and side effects will be evaluated in all participating subjects at baseline and every 3 months. Magnetic resonance scans and optical coherence tomography (OCT) will be evaluated at baseline, year 1, and year 2 of follow-up.

For safety consideration, during stage one of the trial, all the subjects will receive a telephone interview within 1 week after hUC–MSC infusion and then every 2 weeks until the second infusion. The telephone interview will include information on symptoms' change and side effects.

The study schedule is shown in Table 1.

### Data Management

All the study documents from all the centers will be considered highly confidential and will be stored in locked filing cabinets in a room with restricted access. All data will be translated into electronic format and stored in a database. Access to the database will be strongly restricted. The principal investigator and the biostatistician will be able to log into the data set and get full access to the information only upon permission from the head of this study. Data backups will be performed regularly by trial coordinators. If required, data transfer between centers will be encrypted, and any information capable of identifying individuals will be removed.

### Trial Quality Assurance

This study will be implemented according to high-quality standards and will be delivered in accordance with the present trial protocol, which will not be amended unless any SAE occurs during its implementation. All the research staff, including investigators, research assistants, and outcome evaluators, will be trained in advance to be able to competently administer all the items as per the protocol. Once the clinical trial begins, an independent trial inspector will visit each study site monthly and will be responsible for reviewing the following: overall research progress and integrity, adherence to the selection criteria for all the included subjects, compliance with the scheduled intervention for each participant, compliance with national regulations, and the handling of practical problems. Moreover, this trial inspector may occasionally provide suggestions to the principal investigator, who will make any final decisions about trial modifications, continuation, or termination.

### Statistical Analysis

The Kolmogorov–Smirnov Z test will be used for checking data normality. Categorical variables will be summarized as counts (percentage) and continuous variables as the means (standard error, SE) or medians (interquartile ranges, IQR), if not normally distributed. For the primary endpoint of the first time of recurrence, survival analysis will be conducted to analyze between-group differences. The Kaplan–Meier estimates for time of recurrence are presented for all groups. Hazard ratios for the comparison of between groups and 95% CIs were calculated with the Cox proportional-hazards model. Prespecified subgroup analyses of the primary outcome were stratified by, EDSS score at baseline, disease duration, age at randomization, the total number of previous relapses, number of relapses 2 years before randomization, and regular treatment. For secondary outcomes, statistical comparisons between the groups will be performed using Student's *t*-test or the Mann–Whitney U test for continuous variables, as well as the chi-square and Fisher's exact tests for categorical variables, as deemed appropriate. Correlations between continuous variables will be assessed by Pearson's correlation coefficient or Spearman's correlation coefficient. All missing data were not imputed in this study.

In this study, two analysis sets will be required. For the safety set (SS) analysis, all safety indicators will be obtained from those who have undergone at least one dose of hUC–MSC infusions. For the effectiveness analysis set, the intention to treat (ITT) analysis set will be used.

Lan–DeMets alpha-spending function with an O'Brien–Fleming boundary will be used to control the family-wise of type I error. Inverse normal combination test will be used to combine data from stages 2 and 3 in the final analysis. An independent Data and Safety Monitoring Board (DSMB) will review and evaluate the accumulated study data for participant safety, study conduct, and progress at each stage of the study. Only members of DSMB could have access to the data and results of the analysis. The Ethics Committee will be notified of any amendment to the study protocol. DSMB can make recommendations to terminate the study based on one of the following conditions: a significant difference in terms of effectiveness between groups; a significant risk-benefit ratio in one group; low degree of success in a reasonable period (such as poor compliance, low incidence of endpoint events). The advice of the DSMB meeting will be shared with the steering committee of the trial.

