The first stage of the trial, which will last 24 months, is an open-labeled study and will be carried out in the leading center only. The first stage aims to evaluate the safety of the infusion of hUC–MSC in NMOSD patients. Patients (*n* = 30) will be treated with three different doses of hUC–MSC. According to the process of enrollment, the first to the tenth participant is in the low-dose group (*n* = 10, 1 × 10^6^ MSC / kg·weight); the eleventh to the twentieth participant is in the medium-dose group (*n* = 10, 2 × 10^6^ MSC / kg·weight); the twenty-first to the thirtieth participant are in the high-dose group (*n* = 10, 5 × 10^6^ MSC / kg·weight). The study starts from the low dose. Only when the lower dose group ends the observation period of 3 months, the study will proceed to a higher dose group. In case of unacceptable toxic reaction occurs in the dose escalation, the study will be ended immediately. In relation to safety considerations, before enrolling the patients in the low-dose group, we will give a single medium dose of hUC–MSC to one patient and follow-up the therapy for one year. The outcome of this dosage will be used only for safety evaluation, not to evaluate the therapy's effectiveness.The second and third stages of the study protocol are part of the multi-center double-blinded randomized clinical trial. The second stage, which aims to screen out the optimal dosage, will last for 24 months and will be carried out in six centers (one leading center and five branch centers). Patients (*n* = 160) will be randomized into four groups: the low-, medium-, high-dose groups, and the controlled group (*n* = 40, respectively). In the second stage, we were seeking to determine the ‘optimal biological dose.’ The dose that allows reaching the optimal efficacy-toxicity trade-off is further selected and recommended to stage 3. The third stage, which aims to evaluate the effectiveness, will last for 24 months and will be developed in six centers. Patients (*n* = 320) will be randomized into two groups: the optimal dose group (*n* = 160) and the controlled group (*n* = 160). The third stage aims to evaluate the effectiveness and safety of hUC–MSC for NMOSD patients. The study flow chart is shown in Figure 1.

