### Primary and Secondary Efficacy Endpoints

The primary study endpoint is defined as the first time of recurrence. The recurrence should meet all the following four requirements: occurrence of new symptoms or deterioration of original symptoms; symptoms lasting for more than 24 h; more than 30 days from the last recurrence; no other reasons to explain the recurrence.

Secondary endpoints include the times of recurrence, EDSS scores, MRI lesion numbers, OSIS (Opticospinal Impairment Scale) scores, Hauser walking index, and SF-36 (quality of life short Form-36) scores. MRI lesion numbers refer to the total numbers of the lesions on T2-weighted images of the brain, the cervical, and the thoracic spinal cord, respectively. The SF-36 questionnaire is one of the most widely used qualities of life measures and it has been translated and validated in China (28). It has eight multi-item domains including physical functioning, social function, role limitations related to physical problems, role limitations related to emotional problems, mental health, vitality, bodily pain, and general health perceptions. SF-36 results are presented in two categories of physical component summary (PCS) and mental component summary (MCS). EDSS scores, OSIS scores, Hauser walking index, and SF-36 scores will be assessed every 3 months.

Exploratory endpoints include: serum lymphocyte subsets (T helper cells, T suppressor cells, Natural Killer cells, and B lymphocytes), cytokines (Interleukin-2,4,6,10,17A, TNF-α, and IFN-γ), complements, serum anti-AQP4 antibody titers, average retinal nerve fiber layer (RNFL) thickness, etc.

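### Mean (SE) does not describe patient spread, and the Kolmogorov–Smirnov check and unadjusted tests are better replaced by one pre-set, baseline-adjusted method per scale (minor)

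*Protocol article*

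**What the plan says.** All the statements on method are in the Statistical Analysis section of the protocol article.

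- Normality: "The Kolmogorov–Smirnov Z test will be used for checking data normality". No significance level is given. Nor does the text say whether the check is run by arm, by stage or on pooled data, or whether it is corrected for estimated parameters.
- Description: "continuous variables as the means (standard error, SE) or medians (interquartile ranges, IQR), if not normally distributed". The SD is not mentioned.
- Secondary comparisons: "Student's *t*-test or the Mann–Whitney U test for continuous variables", with the choice between them left to judgement. Both are unadjusted two-group tests.
- Combination: "Inverse normal combination test will be used to combine data from stages 2 and 3 in the final analysis".

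The endpoints concerned are in Primary and Secondary Efficacy Endpoints: "Secondary endpoints include the times of recurrence, EDSS scores, MRI lesion numbers, OSIS (Opticospinal Impairment Scale) scores, Hauser walking index", and SF-36. Study Design gives the arm sizes: 10 per dose cohort in stage 1; in stage 2 "the low-, medium-, high-dose groups, and the controlled group (*n* = 40, respectively"); in stage 3 "the optimal dose group (*n* = 160) and the controlled group (*n* = 160"). Table 1 schedules EDSS, OSIS, Hauser index and SF-36 at screening and at every visit from month 3 to month 24.

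**The concern.** The two descriptive options are not alternatives to each other. An IQR describes patients, whereas an SE describes an estimate. A reader who takes the SE for spread would think stage 3 patients more alike than stage 2 patients merely because there are more of them.

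The normality check has a separate weakness. The usual Kolmogorov–Smirnov critical values assume that the mean and SD of the reference normal are known. When they are estimated from the same sample, the test is far too conservative, and whether it rejects depends heavily on n. EDSS, OSIS and the Hauser index are ordinal scores, which is known before any data arrive, so nothing about their handling needs to wait for a test of normality.

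Finally, the stated secondary tests make no use of the screening values. What is at stake is the readability of descriptive tables and the precision and consistency of the secondary comparisons.

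**Working it through.** The plan gives no figure of its own to reproduce here.

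**1. SE against SD.** SE/SD = 1/√n, at the arm sizes in Study Design:

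| n per arm | SE/SD |
|---|---|
| 10 (stage 1) | 1/√10 = 0.32 |
| 40 (stage 2) | 1/√40 = 0.16 |
| 160 (stage 3) | 1/√160 = 0.08 |

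For the same SD, the printed figure halves from stage 2 to stage 3, since √(160/40) = 2. With the 20% loss assumed in Sample Size Estimation (32 and 128 per arm) the values are 0.18 and 0.09, and the ratio is still 2.

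Study Design gives 160 + 320 = 480 patients for stages 2 and 3, while Sample Size Estimation gives 400. One reading that reconciles them is that stage 3 includes the 80 stage 2 patients on the selected dose and control. That leaves 160 − 40 = 120 new patients per arm, SE/SD = 0.09, and a ratio of √(120/40) = 1.7.

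**2. How the uncorrected check behaves.** The 5% level and all distribution shapes are assumptions, because the documents give none. Each sample is standardised by its own mean and SD and compared with the standard Kolmogorov–Smirnov limit.

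| Assumed data | Rejected, n = 40 | Rejected, n = 160 |
|---|---|---|
| Normal | about 0.02% or less | about 0.02% or less |
| EDSS-like, gamma (shape 3, scale 1.2), half-point steps, limited to 0–8 | 4% | 92% |
| EDSS-like, three beta shapes, half-point steps | 0.4% to 3% | 43% to 92% |
| Hauser-like, integers 0–9, right-skewed | 21% | 100% |
| SF-36-like, continuous | 0% | 0.5% |

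For the EDSS-like scales the check rarely rejects at the stage 2 arm size and often does at the stage 3 size. At 120 per arm, rejection was 21% to 67% across the beta shapes. The Lilliefors correction restores the level on normal data (4.4% at n = 40, 4.6% at n = 160) but not independence from n: the middle beta shape gives 52% at n = 40 and 100% at n = 160.

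**3. What selection by the check would cost.** The rule tested uses Mann–Whitney if either arm fails the uncorrected check, and otherwise the t-test. It was applied to the gamma-based EDSS-like scale limited to 0–8, with 4,000 runs per case and a simulation error of about 0.3 to 0.4 points on type I error.

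| | n = 40 per arm | n = 160 per arm |
|---|---|---|
| Type I error, selected by check | 5.0% | 5.7% |
| Type I error, always Mann–Whitney | 4.6% | 5.7% |
| Power for an assumed 0.6-point shift, selected by check | 26.7% | 81.9% |
| Power, always Mann–Whitney | 29.4% | 81.9% |

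The loss is 29.4 − 26.7 = 2.7 power points at 40 per arm and none at 160. Type I error does not move beyond simulation noise.

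**4. What baseline adjustment offers.** In a linear model, adjusting a follow-up score for its screening value multiplies the residual variance by about 1 − ρ², where ρ is the correlation between the two. The documents do not give ρ, so the gain is not quantified here.

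**The case against.** The strongest defence has four parts.

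- The SE is labelled and arm sizes will be reported, so any reader can compute SD = SE × √n. This stands: no information is lost and no inference changes. It does not make the SE a suitable descriptive statistic.
- A reader might infer that the Kolmogorov–Smirnov result decides between the t-test and Mann–Whitney, separately in each stage, so that one endpoint will be analysed in two ways before the stages are combined. The documents do not support that. No sentence ties the choice of test to the check. Its link to the summary is only implied by adjacent sentences, and a single pooled check would not produce the discrepancy.
- A reader might also infer from the rejection rates that secondary results would be seriously distorted. Step 3 shows otherwise, at least for the shape tested. All the shapes are assumed, and the contrast is weaker if stage 3 adds only 120 new patients per arm.
- Detail by scale may be left to an analysis plan that is not shown. Its absence here is therefore no fault. The SE, the named check and the unadjusted tests, however, are stated choices, and those can be improved.

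**Conclusion.** The point holds as a minor one. That mean (SE) is the wrong descriptive pair rests on the text and on 1/√n alone: the printed figure is 0.16 SD at 40 per arm and 0.08 SD at 160 per arm, whatever the patients are like.

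That the uncorrected check is badly calibrated is a general property of the test, confirmed by simulation at an assumed 5% level. Different handling of the same ordinal scale in stages 2 and 3 is only a possibility. It requires that the check be used as a selector within each stage, and even then the measured cost is under 3 power points in stage 2, with no material change in type I error.

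A baseline-adjusted method fixed for each scale is nevertheless a better choice than the stated unadjusted tests, because the screening values are already collected. The primary endpoint, analysed by Kaplan–Meier and Cox, uses neither the SE summary nor the normality check and is untouched.

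**What to change.** In Statistical Analysis:

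1. Summarise continuous and ordinal variables by mean (SD) together with median (IQR). Keep SE or 95% CI for treatment differences.
2. Remove the Kolmogorov–Smirnov check as a means of choosing a summary or test.
3. Replace the unadjusted t-test or Mann–Whitney comparisons with one method per scale, the same in stages 2 and 3 and adjusted for the screening value: a rank-based or ordinal method for EDSS, OSIS and the Hauser index, and a linear model for the SF-36 physical and mental component summaries.

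The cost is wording only. Table 1 already schedules the screening assessments needed, and neither data collection nor sample size changes.
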